### **3.05 Sample size estimate**

The following formula will be used;  $n = [Z_{\alpha} \sqrt{2p_1(1-p_1)} - Z_{\beta} \sqrt{p_1(1-p_1) + p_2(1-p_2)}]^2 / (p_1 - p_2)^2$ , (Dawson & G Trapp, 2004) where 'n' is sample size per group 'Zα' is the critical value of the Normal distribution at 'α', 'Zβ' is the critical value of the Normal distribution at 'β' and 'p1' and 'p2' are the expected sample proportions of the two groups.

Assuming 95% of the cases of depression are missed in primary care practice by selective screening (Jenkins et al., 2013) and we would like to notice a 10% reduction in the cases missed (Pignone et al., 2002).

$$(P_1 - P_2) / P_1 = 0.1$$

$$P_2 = P_1 - (P_1 * 0.1)$$

$$P_2 = 0.95 - (0.95 * 0.1) = 0.855.$$

$$n = [Z_{\alpha} \sqrt{2p_1(1-p_1)} - Z_{\beta} \sqrt{p_1(1-p_1) + p_2(1-p_2)}]^2 / (p_1 - p_2)^2$$

$$n = [1.96 \sqrt{2 * 0.95(1-0.95)} - (-1.282) \sqrt{0.95(1-0.95) + 0.855(1-0.855)}]^2 / (0.95 - 0.855)^2$$

$n = 142.74 \sim 143$  PLHIV per group and 286 in two groups

Catering for non-response at 20% per group,

$$0.20 * 143 = 28.6 \sim 29.$$

Therefore, a total sample size of 344 patients will be enrolled for the study with 172 PLHIV per group.

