### 3.11 Data analysis

Skewed data will be summarised using median and quartiles while mean and standard deviation will be used to summarise non-skewed data.

The trial data will be analysed on an intention to treat analysis basis.

Two-Sample Z-Test for proportions will be used to test the single difference between proportions of cases detected in the two study arms (Dawson & G Trapp, 2004) if the data meets the conditions for the statistic otherwise chi square statistics or Fisher's exact test will be used to answer the objective. Missed cases proportions in a group will be calculated as follows,

$$Z = \frac{\hat{p}_1 - \hat{p}_2}{SE} = \frac{\hat{p}_1 - \hat{p}_2}{\sqrt{\hat{p}(1-\hat{p})\left(\frac{1}{n_1} + \frac{1}{n_2}\right)}}$$

$$\hat{P} = (\hat{P}_1 n_1 + \hat{P}_2 n_2) / (n_1 + n_2)$$

Where;

$\hat{P}_1$  is proportion in group one

$\hat{P}_2$  is proportion in group two

$\hat{P}$  is the pooled proportion of  $\hat{p}_1$  and  $\hat{p}_2$

$n_1$  is the sample size of group one

$n_2$  is the sample size of group two.

The estimates' level of significance will be ascertained using the 95% confidence interval and P-value. The estimate will be considered significant if an estimate's confidence interval does not contain the null value and if the p value is less than 0.05.

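### Section 3.05 takes the null variance at 95% alone while the test in 3.11 pools both arms, so the implied 90% power needs 203 evaluable units per group, not 143

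*Protocol*

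**What the plan says.** Section 3.05 (Sample size estimate) begins "Assuming 95% of the cases of depression are missed in primary care practice by selective screening" and plans for a 10% relative reduction, "0.95 - (0.95 * 0.1) = 0.855". Its formula multiplies 1.96 by the square root of 2p1(1-p1), with p1 = 0.95, and 1.282 by the square root of p1(1-p1) + p2(1-p2). The result is 142.74, rounded to 143 "PLHIV per group and 286 in two groups". The next step, "Catering for non-response at 20% per group", adds 0.20 × 143 = 29, giving 172 per group and 344 in total.

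Section 3.11 (Data analysis) plans a two-sample z-test for proportions. In its standard error, p-hat "is the pooled proportion of" the two arms' proportions, weighted by arm size. A result counts as significant when the 95% confidence interval excludes the null value and "if the p value is less than 0.05".

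Section 3.09 (Data collection, measurement of variables) makes the MINI the reference standard and the source of the denominator, namely the depression cases present in each group.

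**The concern.** The sample size formula and the planned test use different variances under the null hypothesis. At a proportion of 0.95 the binomial variance is small. The pooled proportion under the planned alternative lies midway between 0.95 and 0.855, where the variance is clearly larger. A calculation based on the smaller value sizes a test that the protocol does not plan to run, and it makes 143 look sufficient.

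An underpowered comparison matters here because section 1.02 raises the possibility that selective screening detects as many cases at lower workload. A non-significant result could be read as support for that view when the trial had little chance of showing a difference. The non-response step pulls in the same direction, since the enrolled number less 20% falls below the number said to be needed.

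**Working it through.** **Inputs, all from the protocol.** p1 = 0.95, p2 = 0.855, difference 0.095 (squared: 0.009025), critical value 1.96 and power multiplier 1.282 (3.05); two-sided 5% level and pooled standard error (3.11); equal arms; 20% non-response. The multiplier 1.282 corresponds to 90% power.

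**The protocol's own figure.**
- Null term: √(2 × 0.95 × 0.05) = √0.095 = 0.3082
- Alternative term: √(0.0475 + 0.123975) = √0.171475 = 0.4141
- n = (1.96 × 0.3082 + 1.282 × 0.4141)² / 0.009025 = 142.74, so 143. The figure reproduces.

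**The same inputs with the variance of the planned test.**
- Pooled proportion with equal arms: (0.95 + 0.855)/2 = 0.9025
- Variance: 0.9025 × 0.0975 = 0.0880, against 0.95 × 0.05 = 0.0475 in the formula
- Null term: √(2 × 0.9025 × 0.0975) = 0.4195
- n = (1.96 × 0.4195 + 1.282 × 0.4141)² / 0.009025 = 202.87, so 203 per group
- With unpooled variance throughout: (1.96 + 1.282)² × 0.171475 / 0.009025 = 199.70, so 200

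Both standard forms give about 200. The protocol's form also depends on labelling: calling 0.855 p1 turns 143 into 252 (251.59) for the same two-sided comparison.

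**Power of the planned test.** The normal approximation is Φ[(0.095√n − 1.96 × 0.4195)/0.4141]. The exact figure sums the binomial probabilities of all outcomes that the pooled z-test rejects.

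| Evaluable per group | Approximate | Exact |
|---|---|---|
| 138 (172 less 20%) | 76.1% | 78.3% |
| 143 | 77.6% | 79.0% |
| 172 (no loss) | 84.7% | 86.7% |
| 203 | 90.0% | 91.1% |

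**Non-response.** 172 × 0.80 = 137.6, below 143. Dividing out gives 143/0.80 = 178.75, so 179 per group and 358 in total. The shortfall is 179 − 172 = 7 per group. Falling from 143 to 138 evaluable costs 77.6 − 76.1 = 1.5 points of power.

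**What is being counted.** Under 3.09 a unit in the missed-case proportion is a MINI-confirmed case. Section 1.01 gives depression prevalence among PLHIV in Uganda as 8% to 46%. Taking that range as an assumption for MINI-confirmed disorder, and with no loss:
- 0.08 × 172 = 13.8 cases per group, power about 13%
- 0.46 × 172 = 79.1 cases per group, power about 52%

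These two powers come from the same normal approximation and are rough at the low end.

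**The case against.** The best defence is that 3.05 follows a cited textbook formula and evaluates it correctly, so nothing is miscalculated. That is true of the arithmetic, but it does not settle the matter: the protocol fixes the test itself, and that test pools.

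A second objection is that non-response is undefined. Consent is an inclusion criterion, and the procedure is a screening consultation followed by the MINI, with no follow-up schedule. If the 20% means refusals before randomisation, none of the 172 are lost. This stands. It makes the 138 row conditional, and a reader who took 76–78% as the power of 172 evaluable units would be wrong. The figure there is 84.7% (exact 86.7%), still short of 90%.

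Third, the protocol never names 90%. It is an inference from 1.282, though a direct one.

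Fourth, the abstract gives 382 patients, or 191 per group. Fully evaluable, that has about 88.2% power on the same test, so the shortfall would be small. With 20% lost, about 153 remain and power is about 80%. The conflict between 382 and 344, and the 7.5% in the hypothesis against the 10% in 3.05, mean the inputs need reconciling, but neither enrolment figure reaches 90%.

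A reader might also inflate 203 to 203/0.80 = 254 per group, 508 in total, set that against the clinic's roughly 470 patients, and conclude that the design cannot be carried out. The documents do not support the comparison: under 3.09 the 203 counts depressed cases, while 470 counts all HIV-positive patients.

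**Conclusion.** The point holds. Section 3.05 understates the null variance of the test in 3.11 by almost half (0.0475 against 0.0880), so the implied 90% power is not delivered. The requirement is 203 evaluable units per group instead of 143. Power is 77.6% at 143 (exact 79.0%), making the type II error about 21–22% rather than 10%. The variance term is the main cause; adding the 20% instead of dividing it out is a minor error of 7 per group.

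These figures assume 0.95 against 0.855, equal arms, a two-sided 5% level, and 90% inferred from the multiplier. They count MINI-confirmed cases. It is tempting to read 76–78%, or even 85%, as the power of the enrolled sample, but that would hold only if every enrolled patient were depressed. Power for 172 enrolled per group depends on how many are cases and is lower, about 13% to 52% under the assumed 8–46% prevalence.

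**What to change.** In 3.05, replace 2p1(1-p1) with 2·pbar·(1-pbar), where pbar = (p1 + p2)/2, so that the calculation matches the test in 3.11, and state the intended power in words. Divide by 0.80 for non-response and define what non-response means. State that the resulting 203 per group counts MINI-confirmed cases.

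Keep the enrolment and restate the power, computed at the number of cases expected among the enrolled patients, with the assumed prevalence and its range shown. Do not give 76–78% as the power of the enrolled sample. Before recalculating, settle which enrolment total (344 or 382) and which target reduction (10% or 7.5%) apply.

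The cost is a recalculation and one paragraph. The stated power becomes less favourable, and no procedure changes.

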## **CHAPTER ONE**

### **1.00 Introduction**

Depression is the leading cause of disability worldwide with over 300 million people affected (4.4% of the world's population) (UN health agency, 2017). It is one of the most prevalent mental health comorbidities among People Living with Human Immunodeficiency Virus (PLHIV) (Benton, 2008; Okeke & Wagner, 2013), and it is 2 to 3 times more prevalent among PLHIV in Sub-Saharan Africa (SSA) (Charlotte, Dabis, & de Rekeneire, 2017). In 2016, there were 36.7 million PLHIV worldwide accounting for 0.8% of the world's population aged 15-49 years ("Fact sheet - AIDS epidemic status," 2016).

Major depression among PLHIV in the SSA region is estimated to range from 9% to 32% (Charlotte et al., 2017). This burden is in a population with approximately 25.5 million PLHIV ("Fact sheet - AIDS epidemic status," 2016) amounting to 4.2% of the population of the region aged 15-49 year ("WHO | (GHO) data," 2017).

Lack of screening and subsequent treatment for mental health disorders can affect general health, quality of life, adherence to antiretroviral therapy (ART) and retention into care (9) and therefore affecting most stages in the HIV cascade of care. Depression has been associated with treatment failure and the emanation of drug resistant HIV strains (Hartzell, Janke, & Weintrob, 2008) and it is partly attributed to poor adherence to ART (Gonzalez, Batchelder, Psaros, & Safren, 2011). Screening for, and treating depression has been found to improve health outcomes (Gaynes et al., 2015).

About 46% to 50% of cases of depression are missed in primary care settings in developed countries (Caballero et al., 2008) and close to 100% in developing countries (Abebaw, 2017; Jenkins et al., 2013; Udedi, 2014).

In Uganda, the prevalence of HIV stands at 6.2% (WHO, 2017b) but varies in different regions of the country from 8% to 46% (Akena, 2013; Nakimuli, 2011; Nakku, Kinyanda, & Hoskins, 2013).

Though the ability of the MOH recommended strategy of “selective screening” to detect depression cases is not known, selective screening for depression could offer an advantage of less time spent on screening for depression and less work load. However, selective screening for depression may leave other PLHIV with depression not diagnosed given that the criteria does not cover all the risk factors.

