### **1.01 Problem statement**

The prevalence of depression among PLHIV in Uganda varies from 8% to 46% (Akena, 2013; Nakimuli, 2011; Nakku et al., 2013).

In spite of this high burden, depression is not routinely screened for and thus likely to be missed. The failure of health workers to detect the cases of depression is as a result of a number of reasons which include; poor mental health literacy, health worker un awareness, high patient numbers, and shortage of health workers (Chibanda et al., 2016). This leads health workers to focus on what is considered urgent or important.

In addition, signs and symptoms of depression mask or mimic the clinical presentations of other physical illnesses thus leading to diagnosis of the condition (Goodwin, 2006). Depression is also at times mistaken to be a reaction to medical illness. However, though understanding depression is important in diagnosing depression, it is important to note that training alone has not been found to be enough to increase case detection (Reynolds & Patel, 2017).

It is also worth noting that in addition to the primary care workers not understanding the manifestations of depression as a mental illness, the patients too do not understand it and may at times mistake it for demonic possession or witchcraft (Korstanje, 2016; Sanganyado, 2017). As a result, the patients may not take initiative to clearly describe or report it as such during clinic visits.

Depression affects the general wellbeing of PLHIV, it is associated with a low CD4 count, poor adherence, and poor retention in care among others therefore affecting every stage in the cascade of care (WHO, 2017).

Routine screening could potentially be beneficial but there is limited information in this setting to support this, given the additional resources required.

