#### **3.02 The study setting.**

The study setting is Princess Diana Memorial Health Centre IV is a government health facility found in Soroti district found in the north-east of Uganda. Soroti district has a population of 296,833. The prevalence of HIV in north-east Uganda is 3.7%. Princess Diana Memorial Health Centre IV is located in a peri-urban setting within northern division along Soroti-Moroto road. Northern division has a population of 19,382 (UBOS, 2014). Princess Diana Memorial Health Centre IV has a catchment population of approximately 11,500 people. The health unit has approximately 470 HIV positive patients with two clinic days per week with an attendance ranging from 20 to 35 patients per clinic day. The health centre is staffed with two psychiatric nurses serving the mental clinics in addition to the other non-psychiatric staff.

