#### Measurement of variables

Case detection: These will be measured using the PHQ-2 and the PHQ-9 questionnaires and graded using the guide for diagnosis and management of depression adopted from the Ministry of Health guidelines 2016.

The cases missed by the strategies will be detected using the M.I.N.I. It will therefore be used to determine the denominator (cases of depression present) in both groups.

**The PHQ-2** tool is a two-item instrument that inquires about the frequency of depressed mood and anhedonia over the past two weeks. The purpose of the tool is to screen for depression in a first step approach. The PHQ-2 score ranges between 0–6 and those with a score equal or greater than 3 are further evaluated using the PHQ-9.

**The PHQ-9** is a 9-item depression screening instrument that determines the presence and frequency of the 9 core depressive symptoms identified in the DSM-IV over the previous 2 weeks. This tool has been used in sub-Saharan Africa for a number of studies(Akena et al., 2013). Scores range from 0–27, with a score of 10 or higher usually used to indicate the presence of a depressive disorder that would benefit from treatment. The PHQ-9 was developed to be self-administered, however interviewer-administration and telephone administration (Pence et al., 2012) has yielded similar results.

**MINI**—The Mini International Neuropsychiatric Interview (MINI) is a brief, structured diagnostic interview for major psychiatric disorders. The MINI will serve as the reference standard in this study which will be used to determine the cases in the denominator. The MINI modules for major depressive disorder (MDD) will be used for this study.

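### The 143 per group counts depressed cases but is enrolled as PLHIV, so each arm will hold about 12 to 44 cases and power is far below the implied 90%

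*Protocol*

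**What the plan says.** Protocol section 3.05 sets the control proportion with "Assuming 95% of the cases of depression are missed in primary care practice by selective screening" and the effect with "we would like to notice a 10% reduction in the cases missed". This gives p1 = 0.95 and p2 = 0.855. With 1.96 and 1.282 as the normal deviates, the formula returns 142.74, rounded to 143 and labelled as PLHIV per group. Adding 20% for non-response gives 172, and the section concludes: "Therefore, a total sample size of 344 patients will be enrolled for the study with 172 PLHIV per group".

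The outcome in section 3.08 is the percentage of depression cases that are missed. Section 3.09 (Measurement of variables) says of the MINI: "It will therefore be used to determine the denominator (cases of depression present) in both groups". Section 3.04 admits any consenting adult with HIV who attends the clinic and is not too ill; depression is not an entry criterion.

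Two prevalence ranges are given. Section 1.00 states "Major depression among PLHIV in the SSA region is estimated to range from 9% to 32" percent, and section 1.01 states "The prevalence of depression among PLHIV in Uganda varies from 8% to 46" percent. On the site, section 3.02 says: "The health unit has approximately 470 HIV positive patients".

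**The concern.** Both proportions in the formula have depressed patients as their denominator, so the result is a number of depressed patients per group. Section 3.05 changes the unit from cases to PLHIV at the last step, with no division by prevalence. Only the depressed minority of each arm can contribute to a comparison of missed-case percentages.

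If the error stands, the trial does not have the power that its only sample-size justification implies. A null result would be uninformative about the difference the trial was built to find. That matters here because section 1.02 raises the possibility that selective screening detects as many cases at lower workload. An underpowered null could be read as support for that view when it could not exclude the protocol's own target difference.

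**Working it through.** **Inputs.** From section 3.05: p1 = 0.95, p2 = 0.95 − 0.095 = 0.855, deviates 1.96 and 1.282, non-response 20%, 172 enrolled per arm. The significance rule in section 3.11 is "if the p value is less than 0.05". Prevalence is 9% to 32% for major depression (section 1.00) and 8% to 46% for depression in Uganda (section 1.01). I added 20% as an assumed intermediate value; the protocol does not give it.

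**Reproducing the plan's figure.** n = [1.96·√(2·0.95·0.05) + 1.282·√(0.95·0.05 + 0.855·0.145)]² / 0.095² = (0.6041 + 0.5309)² / 0.009025 = 142.74, so 143. Then 143 + 29 = 172 and 2 × 172 = 344. The arithmetic is as printed; the unit is the problem. To find 143 cases among 172 enrolled, prevalence would have to be 143/172 = 83% with no loss at all.

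**Cases, precision and power.** Assessed per arm = 172 × 0.8 = 137.6. Cases per arm m = 137.6 × prevalence. Power is exact: all outcomes of two binomials with m cases each are enumerated, and those the test rejects at the two-sided 5% level are summed. The half-width of the 95% interval for the difference is 1.96·√[(0.95·0.05 + 0.855·0.145)/m].

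| Prevalence | Cases per arm | Power, pooled Z | Power, Fisher | Half-width (points) | Routine-arm missed rate for 80% power (pooled Z) |
|---|---|---|---|---|---|
| 9% | 12 | 5% | 1% | 23 | at most 0.47 |
| 20% (assumed) | 28 | 23% | 7% | 15 | at most 0.675 |
| 32% | 44 | 35% | 20% | 12 | at most 0.75 |
| 46% | 63 | 45% | 32% | 10 | at most 0.785 |

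At 8% prevalence there are 11 cases per arm and power is 4% (Fisher 1%). Every half-width in the table exceeds the 9.5-point target difference. The half-widths are large-sample values and only a rough guide at 12 cases.

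**Most favourable reading.** With 46% prevalence and no loss, 172 × 0.46 = 79 cases per arm. Power is 54% (Fisher 44%).

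**Patients needed for 143 cases per arm,** 2 × ⌈143/prevalence⌉, before non-response:

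- 46%: 2 × 311 = 622
- 32%: 2 × 447 = 894
- 20%: 2 × 715 = 1,430
- 9%: 2 × 1,589 = 3,178

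All exceed the roughly 470 patients at the site.

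**The case against.** The strongest counter-argument is that the true effect may be far larger than the one sized for. Section 2.02 gives sensitivities of 82.9% for the PHQ-2 and 91.6% for the PHQ-9. If the two steps were independent (an assumption), routine screening would detect 0.829 × 0.916 = 76% of cases and miss about 24%. Against 95% missed under selective screening, exact Z-test power is about 98% even with 11 cases per arm. This is fair, and it shows the trial need not be futile. It is not the effect that section 3.05 uses, however, and it also relies on the 95% control rate being right. If a larger effect is expected, section 3.05 should say so.

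The denominator could also be called unsettled. The Scope paragraph of section 1.07 names cases detected as primary and missed cases as secondary, and section 3.11 describes n1 and n2 only as group sample sizes. Taking all enrolled PLHIV as the denominator does not rescue the design. The same effect becomes prevalence × 5% versus prevalence × 14.5% detected, and with 172 per arm the power (normal approximation) is about 13%, 37% and 50% at prevalences of 9%, 32% and 46%.

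Three smaller points stand without changing the conclusion. Loss may be below 20%, since no follow-up visit is described; without loss the cases number about 14 to 79 per arm over 8% to 46% prevalence. At these counts Fisher's test may well replace the Z-test, because 5% of 12 to 63 cases is only 0.6 to 3.2 expected detections in the control arm; that lowers power further. And the formula's null variance is not the pooled variance of the section 3.11 test: even 143 true cases per arm would give about 78% power, and 90% would need 203. That is a separate defect, but it means the patient numbers above are, if anything, too small.

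**Conclusion.** The concern holds. The 143 is a number of MINI-positive cases and has been enrolled as if it were a number of clinic patients. On the protocol's range for major depression, which is what the MINI identifies, and its own non-response figure, each arm will hold about 12 to 44 cases. Power for 95% versus 85.5% missed is then about 5% to 35%, against an implied 90%; that figure follows from the value 1.282 and is not written in words. No prevalence in the protocol, with or without non-response, and neither choice of denominator brings power above about 54%.

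The conclusion is specific to the protocol's stated effect and its 95% control rate. A much larger true difference could still be detected. This must be corrected, because it is the trial's only justification of its size.

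**What to change.** In section 3.05:

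- Relabel the 143 as MINI-positive cases per group.
- Keep the enrolment of 344, since the site cannot supply the hundreds to thousands of patients that 143 cases per arm would need.
- State the expected number of cases per arm over the protocol's own prevalence range, for example 12 at 9%, 44 at 32% and 63 at 46%.
- Replace the implied 90% power with the power those cases give for 95% versus 85.5%, or with the detectable routine-arm missed rate at 80% power.
- State that the main result will be read from the estimated difference and its confidence interval, and that a non-significant result will not be taken as evidence of equal detection.

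The cost is protocol wording and a much less favourable power statement. No extra patients are needed, and randomisation and study conduct are unchanged.
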